## Qualitative analyses

The evaluation of the trial follows a mixed-methods approach. In addition to the quantitative analyses, we will conduct structured and guided interviews with experts who are involved in the care process (e.g., physicians in the primary care setting). Interviews will be recorded and then transcribed verbatim / partially by application of MAXQDA software (version 12.0 or later, VERBI, Berlin, Germany). Analysis of the transcribed material will follow a qualitative content analysis approach [42]. Results of both, quantitative and qualitative data will be analyzed in combination regarding patient-relevant endpoints and process evaluation. The process of the evaluation follows the guidelines of the Medical Research Council 2006 [54].

### Interim analyses {21b}

Not applicable.

### Methods for additional analyses (e.g., subgroup analyses) {20b}

In addition to the intention-to-treat analyses, we will perform subgroup analyses with participants who received the intervention (per-protocol analyses). Further analyses will be performed with specific subgroups of the study sample (e.g., severity of dementia, different home care situations).

### Methods in analysis to handle protocol non-adherence and any statistical methods to handle missing data {20c}

In univariate and bivariate analyses, the number and distribution of missing data will be identified. In multivariable analysis, missing data will be handled using multiple imputation via chained equations, stratified for the respective group.

### Plans to give access to the full protocol, participant-level data, and statistical code {31c}

Information will be provided on request.

## Oversight and monitoring

### Composition of the coordinating center and trial steering committee {5d}

The DZNE is the coordinating center for the InDePendent study. All partners involved in the study will report regularly to the DZNE on the progress within the study. The ICM provides its own team for the objective evaluation of the study results.

### Composition of the data monitoring committee, its role, and reporting structure {21a}

The study is a population-based cluster randomized controlled trial evaluating the efficacy of a multi-component non-invasive intervention in people with dementia with a very low health risk for study participants. For this reason, a data monitoring committee (DMC) is not needed for our study. However, the authors have no competing interests and the results of the study are independent from the sponsor. All study results will be published.

Objective evaluation of the study is conducted by the Institute of Community Medicine, which has an external and independent role to the consortium leader of the trial, the German Center for Neurodegenerative Diseases e.V.

### Adverse event reporting and harms {22}

We will assess and document all adverse events and unintended effects, and communicate them to relevant study participants. However, we consider the specific risks for participating PwD to be very low. No negative effects on the quality of life of PwD as well as disability or other undesired events due to the intervention are to be expected which is supported by previous studies involving DCM interventions [55].

Nonetheless, it could be possible that some participants feel harassed or pressured by the intervention or the repeated contact attempts. To detect possible adverse events, participants will be asked by questionnaires throughout the study as part of the process evaluation.

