## Abstract

**Background:**

A redistribution of tasks between specialized nurses and primary care physicians, i.e., models of advanced nursing practice, has the potential to improve the treatment and care of the growing number of people with dementia (PwD). Especially in rural areas with limited access to primary care physicians and specialists, these models might improve PwD’s quality of life and well-being. However, such care models are not available in Germany in regular healthcare. This study examines the acceptance, safety, efficacy, and health economic efficiency of an advanced nursing practice model for PwD in the primary care setting in Germany.

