**Methods:**

InDePendent is a two-arm, multi-center, cluster-randomized controlled intervention study. Inclusion criteria are age ≥70 years, cognitively impaired (DemTect ≤8) or formally diagnosed with dementia, and living in the own home. Patients will be recruited by general practitioners or specialists. Randomization is carried out at the physicians’ level in a ratio of 1:2 (intervention vs. waiting-control group). After study inclusion, all participants will receive a baseline assessment and a follow-up assessment after 6 months. Patients of the intervention group will receive advanced dementia care management for 6 months, carried out by specialized nurses, who will conduct certain tasks, usually carried out by primary care physicians. This includes a standardized assessment of the patients’ unmet needs, the generation and implementation of an individualized care plan to address the patients’ needs in close coordination with the GP. PwD in the waiting-control group will receive routine care for 6 months and subsequently become part of the intervention group. The primary outcome is the number of unmet needs after 6 months measured by the Camberwell Assessment of Need for the Elderly (CANE). The primary analysis after 6 months is carried out using multilevel models and will be based on the intention-to-treat principle. Secondary outcomes are quality of life, caregiver burden, acceptance, and cost-effectiveness. In total, *n*=465 participants are needed to assess significant differences in the number of unmet needs between the intervention and control groups.

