### Objectives {7}

The overall goal of the intervention is (1) to assess and address patients’ and caregivers’ unmet healthcare needs to (2) improve the health and living situation of the PwD and caregivers by providing individualized, person-centered and advanced dementia care management (DCM). In addition, the InDePendent study will examine the acceptance, safety, efficacy, and efficiency of an ANP model in primary dementia care in Germany. The aim of this study is to evaluate, whether dementia-specific qualified nurses and a redistribution of tasks between nurses and primary care physicians could significantly reduce the number of unmet needs of PwD compared to routine care after 6 months. Additionally, the study aims to improve PwDs’ quality of life and relieve the informal caregiver burden. Finally, the aim is to evaluate the acceptance and cost-effectiveness of the intervention.

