### Outcomes {12}

The primary outcome of the study is the number of unmet needs in the intervention group compared to the waiting-control group 6 months after baseline. Unmet needs will be assessed with the German version of the Camberwell Assessment of Need for the Elderly (CANE). CANE is available in two versions: one for the PwD (if there is no participating caregiver) and one for the informal caregiver (if the caregiver participates in the study). The result of the CANE is a sum of open and unmet needs.

Secondary outcomes include:
Quality of life

The Quality of Life in Alzheimer’s Disease (Qol-AD) will be used to assess participants’ and caregivers’ quality of life [41]. The German version of the Qol-AD is a well-validated instrument for assessing HRQoL in patients suffering from different dementia diseases, especially for those being mild to moderately cognitively impaired [42].
2.Caregiver burden

Caregiver burden will be assessed by using the Zarit Burden Inventory [43].
3.Acceptance of the care model (process evaluation—only in the intervention group)

In addition to the quantitative analyses, we will perform semi-structured, qualitative interviews evaluated by application of qualitative content analysis [44].
4.Overall health status and economic analyses

For the health economic evaluation, health-related quality of life measured by the EQ-5D-5L and the utilization of healthcare services and informal care measured by the Resource Utilization in Dementia Questionnaire (RUD) [45] and the Questionnaire for Health-Related Resource Use in an Elderly (FIMA) [46] will be assessed.

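### The only named method of eliciting adverse events sits in a process evaluation labelled intervention-only, so as written a comparison of elicited events with usual care would be missing or biased

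*Protocol article*

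**What the plan says.** **Aim.** Objectives {7} states that "the InDePendent study will examine the acceptance, safety, efficacy, and efficiency of an ANP model in primary dementia care in Germany". The abstract's Background says the same: "This study examines the acceptance, safety, efficacy, and health economic efficiency of an advanced nursing practice model for PwD".

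**General commitment.** Adverse event reporting and harms {22} opens with a promise not limited to either arm: "We will assess and document all adverse events and unintended effects, and communicate them to relevant study participants".

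**Method.** The same section then raises the possibility that some participants feel pressured by the intervention or by repeated contact attempts, and names its means of detection: "To detect possible adverse events, participants will be asked by questionnaires throughout the study as part of the process evaluation".

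**Where the process evaluation runs.** In Outcomes {12} the third secondary outcome is headed "Acceptance of the care model (process evaluation—only in the intervention group".

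**Data gathered in both arms.** Outcomes {12} lists quality of life, EQ-5D-5L and "the utilization of healthcare services and informal care measured by the Resource Utilization in Dementia Questionnaire (RUD", together with FIMA. Plans for assessment and collection of outcomes {18a} combines mortality with health utilities to form QALYs, and schedules the 6-month assessment in both groups.

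**The concern.** Evidence on safety is part of why the trial exists. Background and rationale {6a} says that advanced nursing practice is legally possible in Germany only within research that evaluates, among other things, its safety. The Discussion expects the results to inform a legal framework. Some nurse tasks are to be done without consulting the physician first (Intervention description {11a}).

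If adverse events are actively asked about in one arm and left to spontaneous report in the other, the counts are not comparable. The arm that is asked will tend to show more events, which could make the nurse-led model look less safe than it is. If controls contribute no elicited events, there is no comparison to make. Neither problem can be repaired at analysis, because answers to questions never put to controls during their usual-care period cannot be recovered later.

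**Working it through.** The protocol states no figure for safety, so there is nothing to reproduce. The check sets the sections side by side.

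1. **Is safety an aim?** Yes, in the abstract and in Objectives {7}.
2. **How are adverse events found?** Section {22} commits to documenting all of them but attaches no method to that sentence. The only method it gives is questionnaires within the process evaluation.
3. **Who is in the process evaluation?** Outcomes {12} says the intervention group only. Section {22} speaks of participants in general, throughout the study. The two do not agree on their face.
4. **Could controls be reached later by the same route?** Only after the period that matters. Explanation for the choice of comparators {6b} has the waiting-control group change to the intervention after 6 months. A process evaluation tied to the intervention would therefore reach them after their usual-care period had ended.
5. **How many participants does this concern?** Sample size {14} plans 310 waiting-control and 155 intervention patients, 465 in all. On the one-arm reading, the group without elicited events in the comparison period is 310/465 = 66.7%. This is the size of the comparator, not an estimate of bias.
6. **Would spontaneous reporting even things out?** Probably not. Strategies to improve adherence {11c} has nurses in continuous close contact with intervention patients. For controls, the assessments scheduled in {18a} are baseline and 6 months. Events volunteered without prompting would also be picked up more readily in the intervention arm.
7. **What is available in both arms?**
   - Mortality enters the QALYs, which are compared between groups.
   - QoL-AD, EQ-5D-5L, RUD and FIMA are collected in both groups.
   - Section {18b} has discontinuation of participation documented in the study software without limiting this to one arm. Section {11b} lists death and a move to a nursing home among the reasons for stopping or modifying the intervention.

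Steps 2 to 4 give the conflict. Step 7 shows that it concerns elicited adverse events, not every safety-relevant measure.

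**The case against.** The strongest reply is that the one-arm reading is an inference. The general promise in {22} covers all adverse events and both arms. The intervention-only label is a parenthesis in the heading of the acceptance outcome, and acceptance can be asked only of people who received the model. The sentence on questionnaires follows directly after a worry about feeling pressured by the intervention, so it may have been meant for that narrow harm. No section says that controls are not asked.

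Much of this stands. A reader might infer that controls are certainly never asked about adverse events; the text does not settle that, and the accurate description is a conflict between two sections. A reader might also infer that safety cannot be compared with usual care at all. That is not supported either, since deaths, quality of life and service use are collected in both arms.

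It can also be said that adverse-event forms and safety tables are commonly left to a full protocol or analysis plan that is not shown. That is fair, and the absence of a named safety outcome carries no weight here.

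What the reply does not remove is the stated restriction. The general promise names no method, the method that is named uses the same term that Outcomes {12} confines to one arm, and repeated contact attempts could trouble controls as well. A restriction on who is asked is a matter of data collection, and an analysis plan cannot undo it.

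**Conclusion.** The point holds in a limited form. Safety is a stated aim and all adverse events are to be documented, but the only elicitation method named belongs to a process evaluation labelled intervention-only. As written, a comparison of elicited adverse events with usual care over the first 6 months would be missing or biased by unequal ascertainment.

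No numerical size can be given, because the protocol states neither adverse-event rates nor reporting rates. The conclusion assumes that the label in Outcomes {12} applies to the process evaluation referred to in {22}. If the full protocol shows that both arms receive the same questions at the same times, what remains is a wording correction. The change is worth making because it is cheap and the loss could not be recovered afterwards.

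**What to change.** 1. Reconcile Outcomes {12} with Adverse event reporting and harms {22}. State that the same general adverse-event questions, covering the same 6-month period, are put to both arms at the existing 6-month assessment.
2. Keep questions about feeling pressured by the intervention within the process evaluation, in the intervention arm only, and report them descriptively.
3. Report by arm the safety-relevant data already recorded: death, move to a nursing home as a recorded reason for discontinuation, and health-service use from FIMA and RUD. Include hospital admissions if those instruments capture them, which the article does not say. Confirm that nursing-home moves are recorded in controls too, since {11b} lists them in relation to the intervention. Give differences with confidence intervals that allow for clustering by practice.
4. If step 1 is not feasible, limit the safety aim in the abstract and Objectives {7} to a description of the intervention arm.

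The cost is a few added questions at a visit that already takes place and one extra table. Controls who have already passed their 6-month assessment would lack the new items, and the report should say how many they are.

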### Frequency and plans for auditing trial conduct {23}

Not applicable

### Plans for communicating important protocol amendments to relevant parties (e.g., trial participants, ethical committees) {25}

We will communicate protocol modifications and relevant process changes to the Local Ethical Committee at the University Medicine Greifswald and to all relevant ethical committees of the study partners. All changes will be noted in the study registration as well.

### Dissemination plans {31a}

We will publish all relevant study results in scientific journals to share our results with the scientific community and allow for scientific discussion. In addition, all study results will be communicated at scientific meetings and conferences by the investigators. Authorship will be shared between persons involved in the study following the current guidelines of the International Committee of Medical Journal Editors (ICMJE). We plan to communicate the study results to the study participants and health service providers. In addition, results will be used for designing and parameterizing further research projects.

## Discussion

The rapid increase of the number of PwD and the existing and growing shortage of primary care physicians are a challenge for health care systems in many countries in the next decades, requiring new and innovative models of care, especially in rural and remote areas [1, 3–5]. Within the InDePendent project, a new model of advanced nursing care will be developed and tested under routine care conditions in the primary care setting of physicians’ networks. Our study aims to identify unmet nursing, medical, psychosocial, pharmaceutical, and social needs and to improve the living and care situation of people with dementia and their relatives through a redistribution of tasks between specialized nurses and primary care physicians.

The results of the InDePendent study will provide evidence on how to reduce unmet needs among people with dementia. This study will provide evidence for both relevant stakeholders and health policy makers. Trial results will provide evidence for the development of a legal framework for innovative care concepts in the primary care setting, which has an eminently important role for the care of PwD. Particularly the study has the potential to introduce an innovative care concept based on cooperation and the redistribution of tasks between specialized nurses and primary care physicians into regular health care in Germany.

The results of the study will help to modify existing guidelines in dementia. Finally, the project aims to relieve the burden on primary care physicians and to expand the role of nurses, who will assume certain tasks, usually carried out by primary care physicians. This could help to increase professionalization in order to render nursing more attractive for young people as well as increase the motivation to stay in the job for more experienced colleagues. Both are urgently needed to correspond to the growing healthcare challenges resulting from the demographic change. Since the trial will be conducted under real-life conditions in the primary care setting, external validity will be high and the results of the trial are likely generalizable to the primary care setting in other regions.

Due to COVID-19, recruitment took place under difficult conditions. In order to avoid personal contact during the study, a telephone or online video-conference-based survey is offered as an alternative method for data collection.

## Trial status

This is the protocol version 2.0, 2 May 2021. Enrolment into the study started on 1 January 2021 and is estimated to continue until the end of June 2022.

## Data Availability

Information will be provided on request.

## Abbreviations

DCM: Dementia care management
GP: General practitioner
VPN: Virtual Private Network
ICM: Institute for Community Medicine
IMS: Intervention-management-system
PwD: People with dementia
ANP: Advanced nursing practice
